### 1.7.4 GMZ2 (GLURP-MSP3) Phase I trials

#### 1.7.4.1 Phase Ia results from “naïve” German adults

The phase Ia trial of GMZ2 vaccine (GLURP + MSP3 hybrid) in Germany involved the administration of 10, 30 and 100µg of GMZ2 malaria vaccine given with Aluminium Hydroxide (Alhydrogel®) as adjuvant. Thirty volunteers in three groups of 10 were randomised to receive 10, 30 or 100µg of GMZ2 subcutaneously administered four weeks apart in a dose-escalating design. Volunteers were followed up for 14 days after each vaccination to monitor adverse events. Blood samples for immunological assays were taken at baseline and 28 days after each vaccination.

All volunteers were seen on Day 84 (four weeks post third dose) and were included in the intention to treat interim analysis. Twenty-nine out of thirty volunteers received all three doses of the vaccine. One volunteer was excluded for reasons unrelated to GMZ2 vaccinations. All vaccinations were well tolerated and no Serious Adverse Events were observed. All local and systemic adverse events were classified as mild or moderate. Most common solicited adverse events were local reactions at the injection site, fatigue and headache. There were no substantial changes in haematological and clinical chemistry results. Preliminary conclusion was that at all the three different doses used in the trial, the GMZ2 vaccines were safe and well tolerated.

Immunogenicity analysis, total IgG against GLURP, MSP3 and the combined vaccine antigen (GMZ2) was determined by ELISA. At all vaccine dose levels (10, 30 & 100µg), there was a significant increase of IgG against all antigens four weeks after the second and third doses. One week after the first vaccination GMZ2 responses were significantly higher in the 100 µg

[figure not shown]

compared to the 10 µg group ( $p=0.003$ ). All other group comparisons yielded no significant difference. On Day 84 vaccine induced IgG against the vaccine antigen (as well as the individual GLURP and MSP3 domains) reached levels comparable to randomly chosen, adult, semi-immune individuals from Lambaréné (medianLambaréné = 0.9 mg/dl, median10 µg GMZ2 = 1.2 mg/dl, median30 µg GMZ2 = 1.4 mg/dl, median100 µg GMZ2 = 1.4 mg/dl).

In conclusion, it was noted that the safety and immunogenicity profile was similar at all vaccine dose levels tested. Thus, using the highest possible safe dose (100µg GMZ2) in the Phase 1b trial in semi-immune African adults in Gabon will allow gradual reduction in dose levels when age de-escalation trials commence in children and toddlers in Africa.

[figure not shown]

**Figure 2:** Total IgG against GMZ2. Levels on the y-axis are in µg/ml. All p-values were calculated using non-parametric methods (Kruskal-Wallis  $\chi^2$ ). Note the significant difference between the 10 and 100 µg groups on D28. D0: baseline values; D28: 4 weeks after first vaccination; D56: 4 weeks after second vaccination; D84: 4 weeks after third vaccination;

#### 1.7.4.2 Phase 1b interim results from Gabonese malaria exposed adults

The phase 1b trial of GMZ2 vaccine is currently ongoing at Lambaréné Gabon. It is a randomised, controlled trial, double-blind trial evaluating the safety and Immunogenicity of 100µg GMZ2 administered subcutaneously versus rabies vaccine at a schedule of 0, 28, and 56 days in healthy Gabonese males aged 18-45 years.

This study enrolled 40 participants in two arms, and volunteers were actively followed up for 14 days after each vaccination to monitor adverse events. Blood samples for immunological assays were taken at baseline and 28 days after each vaccination. All volunteers were seen on Day 84 (four weeks post third dose) and were included in the intention to treat interim analysis. Thirty nine volunteers received all three doses of the scheduled vaccinations. One volunteer was excluded from receiving the third dose when he was diagnosed with pulmonary tuberculosis. All vaccination were well tolerated and no Serious Adverse Events (SAEs) related to vaccines were observed. Overall, five serious SAEs not related to vaccinations have been reported and adequately followed up.

All local and systemic adverse events were monitored and only one solicited local adverse event was reported as grade 3 (severe) and it resolved within 48 hours. No grade 3 solicited systemic adverse events or grade 3 unsolicited adverse events have been observed. The most common solicited adverse events were local reactions at the injection site, fatigue diarrhoea and headache. There were no substantial changes in the biological parameters measured except for one case reported as SAE who had high eosinophilia which is still under investigation, but it had no reported clinical consequences.

**Table 1: Summary of solicited local adverse events (maximum observed grade)**

[figure not shown]

|            | Vaccination 1   |    |   |   | Vaccination 2   |    |   |   | Vaccination 3   |    |   |   |
|------------|-----------------|----|---|---|-----------------|----|---|---|-----------------|----|---|---|
| AE         | Grade/
Total | 1  | 2 | 3 | Grade/
Total | 1  | 2 | 3 | Grade/
Total | 1  | 2 | 3 |
| Site Pain  | 14              | 14 | 0 | 0 | 30              | 30 | 0 | 0 | 17              | 17 | 0 | 0 |
| Erythema   | 0               | 0  | 0 | 0 | 0               | 0  | 0 | 0 | 0               | 0  | 0 | 0 |
| Induration | 2               | 2  | 0 | 0 | 4               | 4  | 0 | 0 | 2               | 2  | 0 | 0 |
| Oedema     | 2               | 2  | 0 | 0 | 0               | 0  | 0 | 0 | 0               | 0  | 0 | 0 |
| Pruritis   | 1               | 1  | 0 | 0 | 1               | 1  | 0 | 1 | 1               | 1  | 0 | 0 |
| Local heat | 1               | 1  | 0 | 0 | 0               | 0  | 0 | 0 | 0               | 0  | 0 | 0 |
| Total      | 20              | 20 | 0 | 0 | 35              | 35 | 0 | 1 | 20              | 20 | 0 | 0 |

Based on these interim safety results, the clinical development team recommended that GMZ2 is safe in malaria exposed adults and should progress to children studies for evaluation of safety and immunogenicity. The immunological results from this study are expected to be available within the first quarter of 2008.

## 1.8 Rationale

### 1.8.1 Risks and benefit to human participants

The sterility of the product and the absence of toxicological effects are guaranteed by the results of the quality controls performed by Henogen and the pharmaco-toxicological study performed by Scantox. Therefore, we are not aware of any factor that should dramatically alter the safety profile of the active ingredients from what has so far been observed.

### 1.8.2 Rationale for adjuvant selection

Aluminium hydroxide, is most widely used and generally accepted for use in human vaccines. Results in other malaria vaccine trials show that good immune responses can be obtained. Moreover, in the phase Ia trial, it has emerged as the best adjuvant among two others that were compared i.e. Montanide and AS02.

### 1.8.3 Rationale for dosage selection

Studies with either MSP3 or GLURP as Long Synthetic Peptides indicate that both peptides induce a dose-dependent immunological response. This study intends to evaluate previously used 100µg of GMZ2 as well 30µg of GMZ2 as this is the first time the product will be tested in children. This approach will allow for identification of any dose dependant toxicity of the product and also determination of the safest dose of the vaccine that is immunogenic in a population close to the targeted Expanded Program of Immunization (EPI) age group.

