## 2 OBJECTIVES

### 2.1 Primary Objective

**To evaluate the safety and reactogenicity** of three doses of 30 and 100µg GMZ2, adsorbed on aluminium hydroxide, in comparison with three doses of the control vaccine (rabies), in healthy Gabonese children aged 1-5 years. This will be done through evaluation of the following:

1. Immediate reactogenicity; defined as any systemic adverse reactions occurring within 30 minutes after each injection,
2. Local and systemic reactogenicity measured from Day 0 to Day 14 after each dose,
3. Any unsolicited Adverse Event resulting in a visit to a physician between each injection and one month after the third dose,
4. Any Serious Adverse Event (SAE) occurring from the inclusion throughout the study.

Biological safety, one month after each vaccination, in reference with the baseline level the following :

1. RBC, haemoglobin, haematocrit, platelets and WBCs
2. Creatinine, ASAT, ALAT, total bilirubin and alkaline phosphatase.

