### 3 STUDY DESIGN

This will be a randomised, controlled, double blind trial with three arms including: 10 children to receive 30µg GMZ2, 10 children to receive 100µg GMZ2 and 10 children to receive rabies vaccine.

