### 8.2 Determination of the Sample Size

The total number of participants will be 30 divided into three groups of 10 each; one receiving 30 µg of GMZ 2, another 100 µg of GMZ2 and the other receiving rabies vaccine (control vaccine). The sample size chosen for this study are in line with similar safety and immunogenicity studies of similar candidate malaria vaccines published in the literature. As a phase I protocol, this study of 30 volunteers is not designed to detect adverse reactions that occur infrequently. Sample size was determined by the requirement to make a preliminary evaluation of inter-group and inter-individual variability, to avoid excessive risk and to allow realistic workload. Statistical significance may not be reached in such a study with low power; however, a non-significant finding would provide justification of the need for a study with greater power.

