## 8.6 Statistical Methods

The analysis shall be descriptive as the sample size does not allow any comparison between groups. For categorical variables, frequency distributions, by vaccination group, will be presented. For continuous variables, box-whisker plots, medians, inter-quartile ranges and ranges will be presented by vaccine group.

The proportion of participants that received three vaccine doses without experiencing (serious) side effects will be estimated by the Kaplan-Meier product-limit method, with time as a discrete variable.

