### 8.7.1 Plans for analysis

A final statistical analysis plan will be agreed upon by the investigators, AMANET and EMVI prior to locking of the database for the final analysis. However, an interim analysis is planned at 28 days post dose 3 (after day 84). This analysis will allow AMANET and EMVI make decisions for the next trial based on the immediate safety profile. This analysis will include information on adverse events by dose and number of vaccinations. Thereafter, the study will continue in a single blind manner for additional safety surveillance and immunogenicity assessment. This additional information will be appended to the study report.

It is anticipated that the results of this study will be presented to the scientific community via oral presentations at meetings and written publications in scientific journals. The data to be presented and the authorship will be discussed between investigators and the sponsor. It is AMANET policy to have the Principal Investigator lead the authorship for work arising from clinical trials, however, the draft manuscript has to be, approved by the sponsor and EMVI prior to any official communication.

The official report of the primary analysis will be submitted through appropriate channels and upon approval by AMANET. This report will contain detailed information about the participants, their tolerance of the vaccines, their side effects and laboratory abnormalities, as well as their overall immune responses to vaccination based on the ICH E-3 and E-9 format.

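### Section 1.8.3 says the trial will identify any dose-dependent toxicity and the safest immunogenic dose, but section 8.6 rules out between-group comparison and 10 children per arm cannot support the claim

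*Protocol*

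**What the plan says.** Section 1.8.3 (Rationale for dosage selection) justifies the two dose arms: "This approach will allow for identification of any dose dependant toxicity of the product and also determination of the safest dose of the vaccine". The sentence goes on to limit the dose to one that is immunogenic, so the stated aim joins safety and immunogenicity.

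Section 2.1 (Primary Objective) sets the safety evaluation of both doses "in comparison with three doses of the control vaccine (rabies), in healthy Gabonese children aged 1-5 years".

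Section 3 (Study Design) fixes the arms: "10 children to receive 30µg GMZ2, 10 children to receive 100µg GMZ2 and 10 children to receive rabies vaccine". Section 8.2 explains the size: "Sample size was determined by the requirement to make a preliminary evaluation of inter-group and inter-individual variability". It also states that "this study of 30 volunteers is not designed to detect adverse reactions that occur infrequently", and that power is low. It gives no effect size, significance level or power.

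Section 8.6 (Statistical Methods) says: "The analysis shall be descriptive as the sample size does not allow any comparison between groups". The safety analyses that the protocol does name are:
- frequency distributions by vaccine group (8.6);
- 95% confidence intervals for adverse-event incidence within each group (synopsis, Statistical Methods);
- Kaplan-Meier estimates of the proportion completing three doses without side effects (8.5, 8.6);
- a one-sample, one-sided test of serious adverse reactions with an alternative above 25%, whose stated null is nevertheless equal frequency in all three groups (8.6.1).

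On use of the results, section 8.7.1 says of the Day 84 analysis: "This analysis will allow AMANET and EMVI make decisions for the next trial based on the immediate safety profile". Section 3.1 likewise ties the Day 84 results to the go criteria for the next trial in children.

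**The concern.** Identifying a dose-dependent toxicity, and saying which dose is safest, both require setting 30 µg against 100 µg. Section 8.6 says the sample size permits no such contrast, so the two sections cannot both stand.

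The same bar reaches the primary objective. A comparison with rabies vaccine is promised, yet no between-group estimate of reactogenicity is planned.

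What is at stake is the Day 84 report. It describes adverse events by dose and informs the next paediatric trial. Section 1.8.3 would give textual support for reading a small difference in counts as a dose effect, or similar counts as the absence of one. The report would carry no interval for the difference to temper either reading.

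**Working it through.** **1. The plan's own figure.** Section 8.2: "The total number of participants will be 30 divided into three groups of 10 each". 3 × 10 = 30, which agrees. With no rate, effect, level or power stated, there is nothing further to reproduce.

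**2. Inputs.** n = 10 per dose arm comes from sections 3 and 8.2. The protocol gives no expected reaction rates for GMZ2 in children, so the rates below are assumptions shown as a range. Children are treated as independent, with one yes/no reaction each.

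**3. Power to show a dose difference.** Let X and Y be the counts at the higher-rate and lower-rate dose, with X ~ Bin(10, p_high) and Y ~ Bin(10, p_low). Power is the sum of P(X = x)·P(Y = y) over all pairs (x, y) whose one-sided Fisher p-value is at most 0.05. That region starts at 4/10 against 0/10 (p = 0.043), 6/10 against 1/10 (p = 0.029) and 7/10 against 2/10 (p = 0.035).

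| Lower rate | Higher rate | Power |
|---|---|---|
| 10% | 30% | 14% |
| 10% | 40% | 29% |
| 20% | 50% | 25% |
| 10% | 69% | 81% (68% gives 79%) |

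So against 10%, about 69% is needed to reach 80% power. The test is used here only as a yardstick for what 10 v 10 can distinguish; the protocol does not plan it.

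**4. Seeing a reaction at all.** P(0 of 10 | rate 10%) = 0.9^10 = 0.349, or 35%. After 0/10, the exact two-sided 95% upper limit is 1 − 0.025^(1/10) = 0.308, or 31%.

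**5. Simply comparing the two counts.** The protocol sets no rule for ranking the doses. If a reader nevertheless compared the raw counts, then with equal true rates p in both arms

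P(counts differ) = 1 − Σ P(X = x)², with X ~ Bin(10, p) and x = 0 to 10.

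| p | 1% | 5% | 10% | 20% | 30% | 50% |
|---|---|---|---|---|---|---|
| Counts differ | 17% | 54% | 69% | 78% | 81% | 82% |

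For common reactions, a difference in counts is therefore what one expects even when the doses are equally reactogenic. For rare events the figure falls because both arms often show the same count, usually zero.

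**6. Do the planned analyses supply the contrast?** Frequencies, within-group intervals and Kaplan-Meier estimates each describe one arm. The test in 8.6.1 has a between-group null, but a one-sample test against 25% does not compare arms, and it concerns only serious adverse reactions. None of them estimates 100 µg minus 30 µg, or either dose minus rabies, for reactogenicity.

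**The case against.** The strongest reply is that the limitation is already disclosed. Section 8.2 calls the evaluation preliminary, disclaims infrequent reactions, admits low power and says a non-significant result would justify a larger study. The claim in 1.8.3 sits in the background, and selecting a safest dose is not among the objectives in section 2. This stands in part: the fault is an overclaim that contradicts the statistical section, not a hidden weakness. But 8.2 does not withdraw the claim, and its disclaimer on infrequent reactions conflicts directly with a promise to find any dose-dependent toxicity.

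Three stronger readings are tempting, and the documents do not support them.

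- A reader might infer that the trial will pick a dose by the lower count and so err in some 70–80% of trials. No section sets such a rule, and that range fits only common reactions.
- A reader might infer that comparing counts would miss most real dose effects. The low power above belongs to the Fisher test. Under assumed rates of 10% and 30%, the raw counts fall in the right order 81% of the time, tie 12% and reverse 7%.
- A reader might infer that the report would show no uncertainty. The synopsis provides within-group 95% intervals, so 0/10 would appear with its 31% upper limit. What is missing is an interval for the difference.

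It is also fair to object to the volume of output. Eleven solicited reactions, two severity levels and three contrasts would give 11 × 2 × 3 = 66 intervals at 10 per arm. Detailed tabulation can be left to the statistical analysis plan that 8.7.1 foresees. That argues for a short list. It does not remove the contradiction, because the protocol itself states both the claim and the bar.

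**Conclusion.** The point holds as a contradiction within the protocol. Section 1.8.3 asserts a capability that 8.6 denies and 8.2 undercuts, and the comparative primary objective has no between-group estimate for reactogenicity.

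The size of the gap depends on assumed rates. With 10 per dose, power is 14–29% for the 20- to 30-point differences examined, and only a contrast of about 69% against 10% reaches 80%. These figures assume independent children, one binary reaction and a one-sided 5% Fisher test; a two-sided test would do worse. The condition that the dose be immunogenic does not rescue the claim, since choosing the safest among immunogenic doses still needs a safety contrast.

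The sample size itself is not at fault for a phase I trial. What should change is the claim and the blanket bar on comparison, because they shape what the Day 84 report may conclude.

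**What to change.** 1. **Section 1.8.3.** Say that the study gives a preliminary description of reactogenicity and immunogenicity by dose and that, with 10 children per dose, it can show only very large dose differences. Add that similar observed rates will not be read as absence of dose-dependent toxicity, and that a lower observed rate will not be read as establishing the safest dose.

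2. **Section 8.6.** Replace the bar on any comparison with this: no between-group significance tests on reactogenicity; at the Day 84 analysis, risk differences with exact 95% confidence intervals for 100 µg versus 30 µg and for each dose versus rabies vaccine. Limit these to four summary endpoints: any solicited local reaction, any solicited systemic reaction, any Grade 3 solicited reaction, and any related unsolicited event. Label them descriptive and unadjusted for multiplicity. That makes 4 × 3 = 12 intervals.

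3. **Section 8.6.1.** Reconcile the null hypothesis, the one-sample test and the 25% alternative with each other and with the new wording of 8.6.

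**Cost.** Protocol wording and one small extra table from data already collected, with no change to sample size or procedures. The stated claim becomes less favourable and the intervals will be visibly wide.

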### 1.8.4 Justification for 0, 28, 56 Day Schedule

In this adult trial, we seek to evaluate the safety as has been demonstrated in the adult phase Ia trial in Europe and phase Ib trial in Gabon. The target group for this vaccine is the infant population to be vaccinated through the EPI, which includes immunization of infants at four week-intervals starting at the age of six weeks for oral poliomyelitis vaccine and DTP

[figure not shown]

(Diphtheria-Pertussis-Tetanus) in a 0,1, 2 months order. It is envisioned that ultimately, the EPI would be the only efficient means of delivering a vaccine against malaria in resource constrained areas; therefore, all trials of this product will be done using the 0, 28, 56 schedule.

### **1.8.5 Overview of the GMZ 2 clinical development plan**

The clinical development of the candidate malaria vaccine GMZ2 is to progress in following distinct steps;

- 1) Phase Ia dose-finding and adjuvant-selection trial in malaria naïve adults (at Tübingen, Germany);
- 2) Phase Ib trial in malaria-experienced adults (currently ongoing study);
- 3) Phase Ib study in Gabonese children aged 1-5 years;
- 4) Phase Ib study in a few African adults with the final formulation of GMZ2;
- 5) Phase IIb multi-centre efficacy trial involving the children 1-5 years old; and
- 6) Phase III large multi-centre efficacy trial in children.

## **1.9 Comparator Vaccine: Rabies vaccine**

### **1.9.1 Rationale for rabies vaccine**

Having a comparator vaccine is useful in Phase I trials conducted in malaria-endemic areas, since background immunity and natural exposure to malaria may make it difficult to interpret immunogenicity data. In this setting, rising titres of antibody to GMZ2 could be due to immunization or to natural exposure or both. The use of a control group will permit comparison of immune responses and will result in a clearer interpretation of serological results. While a placebo control group would accomplish this same end, using a vaccine that is beneficial to the participants further increases the benefit to risk ratio, which is always relatively low in a Phase I trial. We have chosen to use rabies vaccine as the comparator for the following reasons: i) benefit for participants who will receive rabies vaccine because they have not received this vaccine, ii) rabies vaccine is rarely used in Gabon and in Africa, iii) rabies vaccine is a protein, which is safe and well tolerated and efficacious, iv) rabies vaccine can be administered in the 0, 1 & 2 month schedule that suits the schedule of the study vaccine.

Among human infections, rabies is believed to be the tenth most common cause of death. Once clinical symptoms have occurred, the disease is almost invariably fatal. In the majority of industrialized countries, human rabies is under control, mainly due to oral vaccination of wildlife and mandatory parenteral vaccination of domestic animals. Rabies is currently an incurable disease. Antiviral agents, interferon and massive doses of rabies immune globulin have been used to treat human cases, but seem only to prolong the clinical course without affecting fatality. However, post-exposure treatment initiated at an early stage using rabies vaccine in combination with rabies immune globulin may be 100% effective in preventing death. Given pre-emptively, modern rabies vaccines produce an antibody response in over 99% of vaccinees.

[figure not shown]

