#### 1.4.1 GLURP antigen

The identification and subsequent cloning of the gene for the *P. falciparum* Glutamate-rich protein (GLURP) stems from the work of Jepsen and co-workers on soluble antigens, the so-called exoantigens (Theisen, 2002, 2000, 1998). These antigens are present in the parasitophorous vacuole of parasitized red blood cells. They become associated with the surface of the merozoite at the time of schizont rupture and they are also present in soluble form in the supernatants of *in vitro* cultures of *P. falciparum* as well as in the plasma of patients with *P. falciparum* malaria (Jepsen, 1980; Wilson, 1969). The importance of these antigens is suggested by the observations that affinity-purified human antibodies to exoantigens can inhibit the growth of *P. falciparum* *in vitro* (Jepsen, 1983) and that exoantigens can induce protective immunity against an experimental *P. falciparum* infection in *Saimiri sciureus* and *Aotus nancymai* monkeys (James, 1991, 1985). The potential protective effect of the exoantigens is further suggested by immuno-epidemiological studies showing that levels of cytophilic subclasses are associated with protection against high levels of parasitemia (Luty, 1994) and with protection against clinical disease (Chumpitazi, 1996). The reverse relationship was found for the levels of non-cytophilic IgM and IgG2 subclasses (Chumpitazi, 1996; Luty, 1994) leading to the hypothesis that development of anti-disease immunity in young children depends on IgM antibodies against exoantigens, whereas the progressive development of antiparasite immunity in older children would be reflected by the switch to exoantigen-specific cytophilic subclasses (Luty, 1994). Finally, it has been proposed that vaccination with the exoantigens is a possible strategy for prevention of disease symptoms in malaria (Playfair, 1990).

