## **3.5 Treatment Assignment Procedures**

### **3.5.1 Randomization Procedures**

Individual participants will be randomized to receive either 30µg or 100µg of GMZ2 or rabies vaccine. Randomization to any of the three groups will be done based on a list of eligible participants identified after screening is completed. The randomization list generated by the statistician will ensure that the random allocation has a fairly even distribution of sex and age in the groups. The randomization list will contain sequential codes linking a study number to a vaccine assignment. Study numbers will be assigned to participants of each cohort in the order in which they are enrolled in the trial. Access to the randomization list will be exclusively limited to the vaccine administrator/pharmacist(s) and the study statistician. These individuals will be unblinded and will not be involved in any of the study participants' evaluation. The independent Local Safety Monitor will also keep one set of the randomization code in a sealed envelope, for the event when emergency unblinding may be required.

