## 5.2 Enrolment/Baseline

When a total of 40 eligible participants are screened, a list with their screening numbers, dates of birth and sex will immediately be generated and transmitted to the study statistician based at the London School of Hygiene and Tropical Medicine. The statistician will then generate a randomisation code list that allocates study ID numbers linked to vaccine allocation. This list will be generated to ensure that an even distribution of age and sex is achieved in each of the three study groups. The statistician will then send the randomisation code list directly to the study pharmacist and local safety monitor via email with a secure password to access the list.

At the site study numbers will be assigned to participants of each cohort in the order in which they come to MRU on the day of the first vaccination. Immediately after the first vaccination, each study participant will receive a photo ID card and a copy of the photo ID will be attached to the CRF folder for each participant. The vaccine and dose that are assigned during the first vaccination will be maintained for second and third vaccinations.

Access to the randomization list will be exclusively limited to the study drug manager(s)/pharmacist(s) and study statistician. These individuals are unblinded and will not be involved in study participants' further evaluation. The Local Safety Monitor will also keep one set of the randomization code in a sealed envelope, in the event that emergency unblinding is required. The reason for any unblinding will be documented as well as the steps to be taken.

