### 8.6.2 Secondary Criteria

The secondary and exploratory outcome measures will not be formally analysed with hypothesis testing. The data from the secondary and exploratory outcome measures will be presented as point estimates with 95% confidence intervals. This will enable comparison of the immunogenicity of the three groups at baseline and each of the three vaccinations. As antibody titres usually display skewed distributions, geometric means (with 95% CI) will be calculated instead of arithmetic means.

[figure not shown]

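### Section 8.6.2 compares immunogenicity across arms by geometric means and names no use of Day 0 titre, age or sex, although the first is measured and the other two are balanced by the allocation list

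*Protocol*

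**What the plan says.** Section 1.9.1 of the protocol explains the comparator by saying that "background immunity and natural exposure to malaria may make it difficult to interpret immunogenicity data"; its remedy is the control group. Section 3.5.1 says the list "will ensure that the random allocation has a fairly even distribution of sex and age in the groups". Section 5.2 repeats this: "This list will be generated to ensure that an even distribution of age and sex is achieved in each of the three study groups". Dates of birth and sex of the screened children go to the statistician for the purpose. Section 5.2 also says that study numbers are handed out on the first vaccination day in order of arrival.

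Section 8.6.2 gives point estimates with 95% confidence intervals for the secondary outcomes, uses geometric means for antibody titres, rules out hypothesis tests, and adds: "This will enable comparison of the immunogenicity of the three groups at baseline and each of the three vaccinations". Section 7.2.1.1 promises mean ratios with confidence intervals but does not say which ratios. IgG is measured on Days 0, 28, 56, 84 and 365 (section 7.2.1.2). On size, section 8.2 says: "The total number of participants will be 30 divided into three groups of 10 each".

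**The concern.** The protocol names background immunity as the obstacle to reading titres, measures it at Day 0, and constrains the allocation on age and sex. The stated method for the three-arm comparison then names none of these. When an allocation factor predicts the outcome, leaving it out of the analysis has one of two costs. If the balance works, the arm difference carries almost none of that factor's variation, but the unadjusted standard error still counts it, so the interval is too wide. If the balance does not work, the interval is honest, but chance differences in the factor remain in the estimate.

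With 10 children per arm, precision is scarce. What is at stake is how clearly the trial can show the ratio of each GMZ2 dose to rabies and of 100 to 30 µg.

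**Working it through.** **Inputs from the protocol.** Three arms of 10, total 30 (3 × 10 = 30, as stated). Ages 1–5 years inclusive (section 3.3), read here as 12 to just under 72 months. Section 8.2 gives no significance level, power, effect or standard deviation, so there is no sample-size formula to reproduce. It says: "Sample size was determined by the requirement to make a preliminary evaluation of inter-group and inter-individual variability".

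**Assumptions.** R² is the share of within-arm log-IgG variance explained by the covariate. The standard deviation (SD) is on the log10 scale. The protocol gives neither, so both are shown as ranges.

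**Width, age balanced, three-arm model.**
- Unadjusted half-width: t(0.975; 27) × SD × √(2/10).
- Age-adjusted half-width: t(0.975; 26) × SD × √(1−R²) × √(2/10).
- Ratio of the two: (2.0555/2.0518) × √(1−R²) = 1.002 × √(1−R²).

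| R² | Width ratio, formula | Change in width |
|---|---|---|
| 0 | 1.002 | about nil |
| 0.10 | 0.950 | 5% narrower |
| 0.20 | 0.896 | 10% narrower |
| 0.30 | 0.838 | 16% narrower |

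Simulation with age-matched blocks gives 0.947, 0.888 and 0.828–0.831 at 0.10, 0.20 and 0.30, hence 5%, 10–11% and 16–17%.

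**Coverage and residual noise.** 30 children, uniform ages, no arm effect, total SD 1, 8,000 runs. Simple randomisation stands in for arrival-order assignment.

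| Allocation | R² | Coverage, unadjusted / adjusted | SD of arm difference, unadjusted / adjusted |
|---|---|---|---|
| Age balanced | 0 | 94.6% / 94.4% | 0.453 / 0.453 |
| Age balanced | 0.10 | 96.4% / 95.4% | 0.415 / 0.415 |
| Age balanced | 0.30 | 97.9% / 94.8% | 0.380 / 0.379 |
| Simple | 0.10 | 94.5% / 95.0% | 0.451 / 0.436 |
| Simple | 0.30 | 95.2% / 95.1% | 0.448 / 0.381 |

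The two costs are therefore alternatives. Under balance the estimate is the same with or without age, and only the interval is inflated. Under simple allocation coverage is right and the estimate is noisier.

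**Which case applies?** The list is built from 40 screened children (section 5.2), 30 are enrolled, and numbers follow arrival. A list balanced on paper need not be balanced among those vaccinated. With no balance, the SD of the mean-age difference between two arms is (60/√12) × √(2/10) = 17.3 × 0.447 = 7.7 months. Day 0 titre is not balanced by design, so the second case applies to it.

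**On the ratio scale.** The factor is 10^(t × SD × √(2/10)), with 18 degrees of freedom for two arms unadjusted and 17 adjusted.

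| Assumed SD | Unadjusted | Adjusted, R² 0.10 | Adjusted, R² 0.30 |
|---|---|---|---|
| 0.3 | ×/÷ 1.91 | 1.86 | 1.73 |
| 0.5 | ×/÷ 2.95 | 2.80 | 2.48 |
| 0.7 | ×/÷ 4.55 | 4.23 | 3.57 |

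**Price of three covariates.** Residual degrees of freedom fall from 27 to 24. The t ratio is 2.0639/2.0518 = 1.006, so the loss is 0.6% if all three are balanced and useless. Chance imbalance adds a factor of about √(1 + 3/(30−3−3−1)) = √(1 + 3/23) = 1.063, giving 1.006 × 1.063 = 1.069. That is about 7% wider at worst, and a simulation agrees (1.069). The same formula for one covariate gives 1.002 × √(1 + 1/25) = 1.022, against 1.021 simulated. In this worst case the model breaks even at a joint R² of 1 − 1/1.069² ≈ 0.13. At a joint R² of 0.30 the interval is about 11% narrower (1.069 × √0.70 = 0.894).

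**The case against.** The strongest reply is that section 8.6.2 is silent rather than wrong. It never says unadjusted, a statistical analysis plan is still to be agreed (section 8.7.1), and covariates for a descriptive endpoint commonly belong there. This stands in part: an adjusted ratio in that plan would contradict nothing. It does not dispose of the point. Section 8.6.2 names a method and says it enables the three-group comparison. Section 3.1 analyses all secondary endpoints at Day 84 for the go decision, while section 8.7.1 ties the analysis plan only to the lock for the final analysis. Nothing requires the covariates to be fixed before Day 84 data are seen.

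A second reply is that section 8.6 calls the analysis descriptive because the sample size allows no comparison between groups, and the synopsis promises only within-group intervals. Those per-group intervals are valid descriptions and should stay. But sections 8.6 and 8.6.2 disagree on whether arms are compared, and if they are, the comparison should use what is known.

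Four stronger readings are tempting and not supported:
- **That intervals are too wide and age noise also stays in every comparison.** The calculation shows one or the other.
- **That the protocol documents an age effect on this endpoint.** Section 1.4.1 reports a hypothesis that "the progressive development of antiparasite immunity in older children would be reflected by the switch to exoantigen-specific cytophilic subclasses". That concerns antibody class against exoantigens, not the level of anti-GMZ2 IgG.
- **That section 1.8.3 asks about the youngest children.** Its phrase, "immunogenic in a population close to the targeted Expanded Program of Immunization (EPI) age group", describes the enrolled 1–5 year population and poses no subgroup question.
- **That the go decision is distorted.** No immunogenicity threshold is stated, and section 8.7.1 links the decision to the immediate safety profile.

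**Conclusion.** The point holds as a matter of precision. The stated comparison leaves out the Day 0 titre and the two allocation factors, all already in hand. For age alone, when balanced, the unadjusted interval for an arm ratio covers about 96% at R² 0.10 and 98% at 0.30. Adjustment narrows it by about 5%, 10–11% and 16–17% at R² 0.10, 0.20 and 0.30, and by nothing at R² 0. If balance fails, coverage is right and the loss appears as extra noise (SD 0.448 against 0.381 at R² 0.30).

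These sizes rest on assumed R² values, uniform ages and a common-variance linear model. With all three covariates the joint R² is what counts, and the gain at a given value is smaller when they are not balanced. No error rate or stated decision rule is affected.

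**What to change.** In section 8.6.2, keep the per-group geometric means with 95% intervals as descriptive output. Add, for log IgG at Days 28, 56, 84 and 365, ratios of geometric means for each GMZ2 dose versus rabies and for 100 versus 30 µg. Take these, with 95% intervals, from one linear model on all children, with log Day 0 IgG, age (continuous) and sex as covariates. State that the covariates are fixed before the Day 84 analysis. A plot of IgG against age by arm is optional and descriptive only.

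Reword section 8.6 so that it agrees with section 8.6.2 on whether arms are compared.

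The cost is one paragraph and one table, with no new data. Three of 27 residual degrees of freedom are spent. If the covariates explain nothing, the loss is 0.6% of interval width when they are balanced and about 7% when balance is left to chance. With 10 children per arm, no further covariates should be added.
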